#### Intellectual disability

With the use of the Hayes Ability Screening Index (HASI) [56], a short screening of a possible intellectual disability of youths is obtained. The HASI, originally developed as a screening test to indicate possible intellectual disabilities among persons who come into contact with the criminal justice system, consists of three tests: 1) a spelling subtest; 2) a puzzle; and 3) a clock drawing test. In addition, the screening consists of four questions regarding already known learning difficulties. The HASI proves to be a valid and reliable screener [57-60].

#### Coping

The short version of the Cognitive Emotion Regulation Questionnaire (CERQ) [61] is administered to identify cognitive coping strategies after having experienced negative life events. The CERQ consists of nine different scales with each two items: self-blame, other-blame, rumination, catastrophizing, positive refocusing, planning, positive reappraisal, putting into perspective and acceptance. Items are measured on a 5-point Likert scale ranging from 1 (almost never) to 5 (almost always). The CERQ has widely been used in research among people with health problems [62]. The CERQ has been translated into other languages, among others Turkish [63] and Pursian [64]. The psychometric features were established among a large adult general population and the Cronbach’s alpha reliability coefficients for the subscales were acceptably high and the CERQ proves to be valid [61].

#### Psychological needs

The basic psychological needs scale [65] is used to measure the theoretical concept of self-determination. The scale consist of three subscales: competence, relatedness and autonomy. The total score reflects the extent to which participants are satisfied with the fulfillment of their basic psychological needs in general. Youths are asked to indicate their agreement with the 21 items on a 7-point Likert scale, ranging from 1 (not true at all) to 7 (definitely true). The scale has been used in many other studies [66]. Adequate factor structure, internal consistency, discriminant validity and predictive validity have been demonstrated among undergraduate students and Greek-speaking exercise participants [67,68]. The external validity of the questionnaire was ascertained by comparing scale scores with other with measures of well-being and worry [67].

#### Care needs

Care needs are assessed using a questionnaire developed by our research centre. The response categories were based on the format of the Short Form Quality of Life and Care questionnaire (QoLC) [69]. Needs are considered on the following 21 domains: housing, self care, finances, searching for work, daily activities, basic skills (reading, writing, calculating), household, transport, family contacts, social contacts, relationship with the children, help for own children, own safety, safety of other people, physical health, mental health, empowerment (assertiveness, self-defense courses), alcohol use, drug use, teeth and nutrition. For each domain, two questions were asked: 1) “Do you want help with . . . ?”, and 2) “Do you get help with . . . ?” The questionnaire has been used in research among homeless youths [6,70] and abused women [71].

#### Care use

Care use is assessed by using a questionnaire developed by our research centre. Youths are asked if they have used different types of care (e.g. psychological help, medical help, addiction treatment) at any time in their live and/or during the last six months and/or last 30 days.

#### Resilience

A positive secondary outcome, resilience, is measured with the Dutch Resilience scale (RS-NL) [72,73]. The Dutch scale consists of two subscales: 1) personal competence; and 2) acceptance of self and life. The 25-items are measured on a 4-point Likert scale, ranging from 1 (strongly disagree) to 4 (strongly agree). The Dutch version appears to be valid and reliable [73,74].

### Sample size and power calculation

To our knowledge no research among homeless youth has been carried out that used this quality of life instrument [39] to measure quality of life as the primary outcome measure. In comparable research among youths, in which a different instrument was used [75], an effect size of .95 was observed. Compared to baseline measurement, youths in the experimental group reported an increase in general life satisfaction of 6.45 (SD=5.89) at nine-month follow-up while controls reported a decrease of −2.25 (SD=11.61). Given that the setting and focus of the present study are different compared to Ferguson and Xie [75], a more conservative effect size was chosen. To calculate the required sample size, a mean improvement in the subjective quality of score of 0.74 (SD=1.48) is assumed. To detect this difference with 80% power (α = .05, two-sided), each group should comprise 63 participants. Considering potential loss of power due to clustering of data in services, power analyses revealed that at least 15–20 participants in each service (ICC = .05) are needed. Thus, taking a maximum of 30% attrition over time into account, 251 participants at baseline, and 178 participants at T1 are required.

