## Methods

### Study design

The effectiveness and fidelity of Houvast are investigated by means of a quasi-experimental research design with two groups and one baseline and two follow-up measurements (Figure 1). Both the intervention group and the control group (‘care as usual’) consist of Dutch services for homeless youth which deliver ambulatory and/or residential care. The services are randomly allocated to the intervention (*n* = 5) or control group (*n* = 5). Stratified randomization is used to ensure that services which deliver ambulant and/or residential care are equally distributed among each group. Randomization of homeless youths was not feasible since entire teams were trained prior to the baseline measurement in the strengths based method. Hence, a quasi-experimental research design is the best feasible design.

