### Data collection

Measurements of primary and secondary outcomes are conducted among youths within the intervention group (*n* = 123) and the control group (*n* = 128) by means of three structured interviews. The first interview (T0) is conducted as soon as possible but within two weeks after the start of ambulant or residential care. Since the average duration of care delivered to homeless youths is three to six months, they are interviewed for a second time (T1) when services end care or when they have received care for a period of six months consecutively. The final follow-up interview (T2) takes place nine months after the first interview. In addition, professionals fill out an electronic questionnaire around T1 to obtain information about their perspective on the working relationship and the quality of life of a particular youth they provide care to. Based on the average number of homeless youths entering the participating services per year, the total period of the data collection is expected to be one year and nine months.

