### Analyses

1) Differences in baseline characteristics (age, gender, education, nationality and ethnicity) between the intervention and control group will be checked by using Chi-square tests, Student’s t-tests and ANOVA's.

2) To examine if the Houvast method proves to be effective or not and to examine additional factors associated with quality of life of homeless youths, a two-level multilevel regression analysis will be used. Since data is clustered – youths are ‘nested’ in services – the analysis will be adjusted for the cluster effect at ‘service’ level. Analyses will be adjusted for potential confounders, such as gender, age, ethnicity, intellectual disability, duration of homelessness and model fidelity.

3) To assess the degree of consensus on the working relationship satisfaction between professionals and youths, a one-with-many design with multilevel analysis will be used. This design addresses the problems associated with non-independence and it accounts for interdependence between professionals and youths.

4) Regarding the fidelity assessment of the strengths based method of each service, all sources (e.g. questionnaires, interviews, observations) will be analysed and by averaging the scores on ten indicators a total score on a 5-point scale will be obtained, whereby a score of 4 reflects a sufficient model fidelity. The total score will also be used as a covariate when examining the effectiveness of Houvast.

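### With ten services and an ICC of .05, the planned 178 youths at T1 give about 69% power for the assumed 0.74-point difference, not the 80% that the sample size paragraph implies

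*Protocol article*

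**What the plan says.** All the sample size inputs are in the protocol article.

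- *Sample size and power calculation* fixes the effect: "a mean improvement in the subjective quality of score of 0.74 (SD=1.48) is assumed". For independent observations it continues: "To detect this difference with 80% power (α = .05, two-sided), each group should comprise 63 participants".
- The same section then turns to power lost through clustering and says that "power analyses revealed that at least 15–20 participants in each service (ICC = .05) are needed". It concludes, with a linking word that makes the totals follow from this step: "taking a maximum of 30% attrition over time into account, 251 participants at baseline, and 178 participants at T1 are required".
- *Study design* sets the number of clusters: "The services are randomly allocated to the intervention (*n* = 5) or control group (*n* = 5").
- *Data collection* gives near-equal arms at baseline: "youths within the intervention group (*n* = 123) and the control group (*n* = 128").
- *Analyses* commits to a two-level model in which "the analysis will be adjusted for the cluster effect at ‘service’ level".

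No power other than 80% is mentioned, and none is given again after the clustering step.

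**The concern.** Whole services are randomised and the analysis will respect that, so the sample has to be judged on its effective size after clustering. The paragraph names an ICC and a cluster size and presents the resulting totals as what is required, but those totals look too small for the ICC beside them. With only five services per arm, each further youth in the same service adds little information.

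This is the only sample size justification for the primary comparison. If true power is well below the implied 80%, a null result will be read as firmer evidence against the method than it is. The Discussion already offers poor implementation as an explanation for a null result and counts the large sample as a strength. Low power would be a further explanation that the paragraph hides.

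**Working it through.** **Inputs.** Difference δ = 0.74, SD σ = 1.48, two-sided α = .05, power 80%, ICC = .05, 15–20 youths per service, 178 at T1 and 251 at baseline (*Sample size and power calculation*); five services per arm (*Study design*). Arms and service sizes are taken as equal, and the 178 at T1 as the number analysed.

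**Step 1: the plan's unclustered figure.** n per group = 2(1.96 + 0.84)² / (0.74/1.48)² = 2 × 7.85 / 0.25 = 62.8, so 63. This reproduces.

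**Step 2: attrition.** 178/251 = 70.9% retained, a loss of 29.1%. This is within the stated maximum of 30%.

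**Step 3: clustering.** With m youths per service:

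- design effect DE = 1 + (m − 1) × ICC
- effective n per arm = 5m / DE
- power = Φ(0.5 × √(effective n / 2) − 1.96)

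At 178, m = 17.8 and DE = 1 + 16.8 × .05 = 1.84. Effective n = 89/1.84 = 48.4 per arm, against the 63 needed. Power = Φ(0.5 × √24.2 − 1.96) = Φ(0.50) = 69%.

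| Youths per service | Total | DE | Effective n per arm | Power (normal) | Power (t, 8 df) |
|---|---|---|---|---|---|
| 15 | 150 | 1.70 | 44.1 | 65% | 54% |
| 17.8 | 178 | 1.84 | 48.4 | 69% | 58% |
| 20 | 200 | 1.95 | 51.3 | 72% | 60% |
| 25.1 | 251 (no attrition) | 2.205 | 56.9 | 76% | 65% |

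The last column is a sensitivity check. It uses a noncentral t with 2 × 5 − 2 = 8 between-service degrees of freedom, a reference distribution that the article does not name.

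**Step 4: what ten services would need.** Setting 5m / (0.95 + 0.05m) = 63 gives 1.85m = 59.85, so m = 32.4 per service, or about 324 analysed (normal approximation). With 8 df the requirement is about 864.

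**Step 5: difference detectable with 80% power at 178.** Normal: (1.96 + 0.84) × 1.48 × √(2/48.4) = 0.84 points. With 8 df the multiplier 2.80 becomes about 3.20, giving about 0.96 points.

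**Step 6: other readings of the inputs.**

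- One-sided α = .05 gives 79% at 178. The text says two-sided, and a one-sided test would need 50 per group, not 63.
- An ICC of .025 gives 80% at 178, but .05 is stated.
- Unequal service sizes lower power: an assumed coefficient of variation of 0.3 gives 67%.

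**The case against.** The strongest reply is that the article never attaches 80% to the 178; the figure stands beside the 63 per group, before clustering. That is true of the wording, and it would be too strong to say that the article states 80% power for the final sample. But the clustering sentence is about offsetting lost power, the totals follow from it, and no other target appears. The implication is plain.

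A second reply is that the planned model may adjust for baseline quality of life and so recover power. An assumed baseline–follow-up correlation of 0.5 would give about 81% (normal) or 70% (8 df) at 178. This has some force: the 69% follows from the stated inputs and need not be the power of the final model. But the article claims no such gain, and the covariates it lists as examples do not include the baseline score.

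Three stronger readings are tempting and not supported.

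- A reader might infer that the attrition step is wrong, because 251 × 0.70 = 176 and 178/0.70 = 255 after rounding up. The 30% is a maximum, and a 29.1% loss respects it.
- A reader might take 58% as the power under the plan's own inputs. It needs a small-sample reference distribution that the article does not specify and that could properly be left to an analysis plan.
- A reader might note that 178/126 = 1.41 and conclude that a smaller ICC or cluster size was used. The article does not show how 178 was reached, so that is conjecture.

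**Conclusion.** The point holds. On the article's own effect size, α, ICC, number of services and T1 sample, power is about 69%. The chance of missing the planned difference is about 31%, where the paragraph implies 20%. No cluster size in the stated 15–20 range reaches 80%, and neither does full retention of all 251.

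The result rests on the usual design effect with equal service sizes, the normal approximation, no gain from baseline adjustment, and 178 analysed. The first two are favourable to the plan: unequal services or a t reference with 8 df would lower the figure, the latter to about 58%. Baseline adjustment could raise it, by an amount the article gives no basis for computing. The unclustered 63 per group and the 251/178 attrition figures are sound.

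**What to change.** Reword *Sample size and power calculation*:

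- State that with ten services, ICC .05 and about 178 analysed, power for a 0.74-point difference (SD 1.48) is about 69%, or about 58% under a t reference with 8 df.
- State that the difference detectable with 80% power is about 0.84 points, or about 0.96 with 8 df.
- Stop presenting 15–20 youths per service as sufficient to offset clustering. At ten services and ICC .05, 80% would need about 32 per service at follow-up (normal approximation).
- If baseline adjustment is expected to recover power, state the assumed baseline–follow-up correlation and recompute.

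Leave 251 and 178 as they are. The cost is a few sentences and a less favourable power statement. Design, recruitment and analysis do not change.

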### Model fidelity

To assess the model fidelity of the Houvast intervention, different assessments are conducted. During a one-day audit by two trained researchers to the service, the following activities are carried out: an interview with the team manager, an interview with the supervisor (in case a supervisor is established), a focus group with homeless youths, a file analysis, and an observation of a strengths based group supervision. Professionals, the supervisor and the team manager all fill out a questionnaire on the implementation of Houvast (e.g. questions about caseload, tasks and activities, use of strengths assessment and recovery plan) before the audit takes place.

Model fidelity is assessed with the fidelity scale of the strength based method. The fidelity scale consists of ten indicators: 1) case manager responsibilities; 2) caseload ratios; 3) supervisor to staff ratio and supervisor; 4) group supervision; 5) strengths assessment; 6) integration of strengths assessment; 7) personal recovery plan; 8) community contact; 9) naturally occurring resources; and 10) hope-inducing behaviours [31,35]. The scale consists of three subscales: structure, supervision/supervisor and clinical/service. Each indicator is rated on a 1 to 5 scale after gathering information from multiple sources. A total fidelity score is obtained by averaging the scores on the ten indicators. Each service receives an extensive report with specific recommendations on how to improve their model fidelity.

### Analyses

1) Differences in baseline characteristics (age, gender, education, nationality and ethnicity) between the intervention and control group will be checked by using Chi-square tests, Student’s t-tests and ANOVA's.

2) To examine if the Houvast method proves to be effective or not and to examine additional factors associated with quality of life of homeless youths, a two-level multilevel regression analysis will be used. Since data is clustered – youths are ‘nested’ in services – the analysis will be adjusted for the cluster effect at ‘service’ level. Analyses will be adjusted for potential confounders, such as gender, age, ethnicity, intellectual disability, duration of homelessness and model fidelity.

3) To assess the degree of consensus on the working relationship satisfaction between professionals and youths, a one-with-many design with multilevel analysis will be used. This design addresses the problems associated with non-independence and it accounts for interdependence between professionals and youths.

4) Regarding the fidelity assessment of the strengths based method of each service, all sources (e.g. questionnaires, interviews, observations) will be analysed and by averaging the scores on ten indicators a total score on a 5-point scale will be obtained, whereby a score of 4 reflects a sufficient model fidelity. The total score will also be used as a covariate when examining the effectiveness of Houvast.

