Some limitations may be mentioned as well. First, due to the complex and unpredictable situation of homeless youth, it may be difficult to motivate them to participate in the follow-up interviews. Most youths leave the service within nine months and locating them to make an appointment for a final interview requires a large investment of researchers. By increasing the financial compensation for their time and effort to complete the interviews, they will hopefully remain motivated. Second, even though youths are interviewed for the first time during the first two weeks after entering the service, there is a small possibility that they were influenced in their scoring on the baseline measurement by whether they entered an experimental or a control service. We will inspect the baseline scores of both groups on significant differences in quality of life and the secondary outcomes, the last follow-up measurement will be conducted at nine months after baseline. Even though it is unique to follow homeless youths for this extensive period of time, a longer time span in which their recovery (or not) would have become more apparent would have been ideal. However, due to practical and financial constraints this was not feasible in the present study.

If the Houvast method proves to be effective in improving the quality of life of homeless youths, the study has strong practical relevance as the quality of work within services for homeless youth could be improved and more professionalized.

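### The baseline comparison of arms uses youth-level tests that ignore the allocation of whole services, so its p-values are too small for any positive intraclass correlation

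*Protocol article*

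**What the plan says.** In the protocol article, Analyses item 1 states: "Differences in baseline characteristics (age, gender, education, nationality and ethnicity) between the intervention and control group will be checked by using Chi-square tests". It goes on to name t-tests and ANOVA. It mentions no allowance for service.

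Elsewhere the article does recognise clustering:

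- Study design says that services were the units allocated, five to each arm, with stratification by type of care (ambulant and/or residential).
- Analyses item 2 says of the effectiveness model that "the analysis will be adjusted for the cluster effect at ‘service’ level".
- Analyses item 3 deals with non-independence between professionals and youths.
- Sample size and power calculation allows for clustering: 15–20 "participants in each service (ICC = .05) are needed".

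The Discussion concedes that T0 scores might be influenced by the kind of service a youth has entered. Its response is: "We will inspect the baseline scores of both groups on significant differences in quality of life and the secondary outcomes". It names no test for this.

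**The concern.** A chi-square test, t-test or ANOVA on individual youths estimates the chance variation between arms from the variation between youths. When services are allocated, chance variation between services also moves the arm means, and these tests leave it out. If youths in the same service are at all alike, the standard error is too small and a nominal 5% test rejects more than 5% of the time when there is no systematic difference.

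The baseline comparison carries more weight here than in an individually randomised trial. Teams were trained before baseline, and youths entered afterwards and were approached by those services' own professionals (Study design; Procedure). Systematic differences in who enrols are therefore possible, and the baseline comparison is where one would look for them. A test that flags differences too often makes ordinary variation between services look like selection. Applied to T0 outcome scores, it could look like an effect of the arm on baseline answers.

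**Working it through.** **Inputs from the protocol article.** There are 5 + 5 services (Study design). Baseline numbers are 123 and 128 youths, 251 in all (Data collection), so the mean per service is 251/10 = 25.1. ICC .05 is stated once, in the power calculation for subjective quality of life. A two-sided α of .05 is stated there too.

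**Assumptions.** The level of the baseline tests is taken as 5%, because none is stated. The ICCs of the five characteristics are not given, so a range is shown. Service sizes are taken as nearly equal, because none are given.

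**The plan's own figure.** The article states no error rate for the baseline tests. Its 63 per group reproduces from its own inputs: 2 × (1.96 + 0.842)² × (1.48/0.74)² = 2 × 7.85 × 4 = 62.8, rounded up to 63. That figure takes youths as independent. The article then recognises that clustering costs power, which is the allowance missing from item 1.

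**False-positive rate of an unadjusted test.** The design effect is DE = 1 + (m − 1) × ICC, with m = 25.1. The unadjusted statistic has variance DE instead of 1 under the null, so the actual two-sided rate is 2 × [1 − Φ(1.96/√DE)].

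| Assumed ICC | DE | 1.96/√DE | Rate per test | Simulated t-test |
|---|---|---|---|---|
| 0 | 1.000 | 1.960 | 5.0% | 4.7% |
| .01 | 1.241 | 1.759 | 7.9% | 7.6% |
| .02 | 1.482 | 1.610 | 10.7% | 10.9% |
| .05 | 2.205 | 1.320 | 18.7% | 18.8% |
| .10 | 3.410 | 1.061 | 28.9% | 28.9% |

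The simulation used 5 + 5 services of 24 to 26 youths (123 against 128), no stratification and 8,000 runs per ICC. For a two-category characteristic, a chi-square test in 10,000 runs gave 18.7–19.0% at ICC .05, or 15.6% with continuity correction.

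**Sensitivity to cluster size.** At ICC .05, 15 youths per service gives DE = 1 + 14 × .05 = 1.70 and a rate of 13.3%. Twenty per service gives DE = 1.95 and 16%. Cluster size matters less than the unknown ICC.

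**What a non-significant result would show.** At ICC .05 the 251 youths carry about as much information as 251/2.205 ≈ 114 independent ones, from only ten allocated units. A non-significant arm difference at T0 therefore leaves room for a real one.

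**The case against.** The strongest reply is that little depends on these tests. The effectiveness analysis is a two-level model with a service effect, and its estimate and type I error do not use item 1. No action is tied to the baseline result. This stands, and it limits the weight of the point.

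Four stronger readings are tempting, and the article does not support them:

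- **A flat 19% false-positive rate.** This takes the ICC from the power calculation for subjective quality of life and applies it to age, gender, education, nationality and ethnicity, for which none is given. It also leaves out the stratification: between-service variation explained by care type is partly balanced across arms, which could lower the rate somewhat. Only the range is defensible.
- **About a 64% chance of at least one false alarm among the five.** The sum 1 − (1 − .187)⁵ ≈ .64, against 1 − .95⁵ ≈ .23 for valid tests, requires ICC .05 for all five and mutual independence. Nationality and ethnicity are unlikely to be independent.
- **Baseline tests that steer covariate choice.** Nothing says so. Item 2 already names gender, age and ethnicity among its adjustment variables. The list is open-ended, but it is not linked to item 1.
- **T0 outcome scores tested as in item 1.** The Discussion names no test and does not refer to item 1. The same fault follows only if the same tests are used.

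It is also fair to say that an unadjusted test does not create an imbalance. A difference between the enrolled groups is real in that sample. What is wrong is the p-value attached to it.

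The omission cannot be left to a fuller plan, because item 1 names its tests and they conflict with the nesting recognised in item 2.

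**Conclusion.** The point holds, with limited consequences. As written, item 1 exceeds its nominal level for any positive ICC. The size is uncertain: about 8% to 29% per test over ICC .01 to .10, at 25.1 youths per service, a 5% level, nearly equal service sizes and no credit for stratification. The direction does not depend on where in that range the truth lies.

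The harm is confined to what is concluded about baseline comparability and, if the T0 outcome scores are tested in the same way, about influence of the arm on those scores. In that second use the check could mislead in both directions: a significant result is weak evidence of influence, and a non-significant one does not exclude it. The primary treatment comparison is not affected.

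**What to change.** In Analyses item 1, replace the youth-level tests with a baseline table by arm and by service, with standardised differences between arms. If tests are wanted, use ones that account for service.

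For T0 quality of life and the secondary outcomes, replace the search for significant differences with the estimated arm difference and its 95% interval, from a model with a service effect and small-sample degrees of freedom suited to ten services. Judge possible influence of the arm from the estimate and the width of the interval.

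The cost is a change of analysis wording, with no new data. The downside is wider intervals and fewer significant baseline differences, which reflects the information that ten services actually provide.

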**Method/Design:**

The effectiveness and fidelity of Houvast will be tested in ten Dutch services for homeless youth which are randomly allocated to an intervention group (*n* = 5), or a control group which provides care as usual (*n* = 5). Measurements of both objective and subjective quality of life and secondary outcomes (mental and physical health, substance use, coping, resilience, psychological needs, care needs, working relationship with the professional and attainment of personal goals) will be conducted among homeless youths (*n* = 251). Youths in both groups will be interviewed by means of a structured interview at baseline, at time of ending care or after having received care for six months (T1) and at nine months after baseline (T2). Model fidelity will be tested around T1.

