The present study aims to examine the effectiveness of Houvast in Dutch services for homeless youth and also to assess the fidelity of this strengths model. Studies that used fidelity scales have found better outcomes when services adhere closely to a model with specified critical components [35-37].

The research questions of the present study are:

1. Is Houvast more effective than care as usual in improving the quality of life among homeless youths?

2. Is Houvast more effective compared to care as usual regarding recovery in terms of mental and physical health, substance use, coping, resilience, psychological needs, care needs, working relationship with the professionals and attainment of personal goals?

3. To what degree is there consensus, between professionals and youths, on the degree of satisfaction with their working relationship?

4. What is the fidelity of the strengths based method and is there a positive association with the effectiveness of Houvast?

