### Care as usual

Youths in the control group receive care as usual. To get insight into care as usual, professionals fill in a questionnaire about education, years of working experience and the caseload. In addition, the contact person of each service in the control group answers general questions about the average intensity of care, coaching and the actual approach or method used.

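### Model fidelity, a score taken after allocation that rates delivery of Houvast, is adjusted for as a confounder in the model that tests whether Houvast works

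*Protocol article*

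**What the plan says.** All places are in the protocol article.

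- **Analyses, item 2.** A two-level regression (youths within services) examines whether Houvast is effective and also which other factors are associated with quality of life. Its adjustment set is: "Analyses will be adjusted for potential confounders, such as gender, age, ethnicity, intellectual disability, duration of homelessness and model fidelity".
- **Analyses, item 4.** After describing the ten-indicator total score, it adds: "The total score will also be used as a covariate when examining the effectiveness of Houvast".
- **Abstract, Method/Design.** On timing: "Model fidelity will be tested around T1".
- **Study design.** Services are randomly allocated, five to each group, and "entire teams were trained prior to the baseline measurement in the strengths based method".
- **Model fidelity.** "To assess the model fidelity of the Houvast intervention, different assessments are conducted". On the source material: "Professionals, the supervisor and the team manager all fill out a questionnaire on the implementation of Houvast".
- **Care as usual.** Besides a staff questionnaire on education, experience and caseload, "the contact person of each service in the control group answers general questions about the average intensity of care". No fidelity audit is mentioned there.
- **Background, research question 4.** Fidelity has its own question, apart from question 1 on effectiveness: "What is the fidelity of the strengths based method and is there a positive association with the effectiveness of Houvast".

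**The concern.** A confounder must not be a result of the allocation. Here services are allocated, the Houvast teams are trained, and fidelity is then scored from things such as the strengths assessment, the recovery plan and group supervision, which are the content of Houvast. The Discussion itself places fidelity between method and outcome when it says that poor implementation could explain a failure to find an effect.

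The arm coefficient of this model answers research question 1. With fidelity held fixed, it compares Houvast with usual care as if both delivered Houvast equally well, which is not the question asked. The plan also leaves open what value a control service takes on this covariate, and the meaning of the coefficient depends on that value. A real benefit could be hidden, or no estimate obtained.

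**Working it through.** **Inputs from the protocol.** Five services per group (Study design); 123 and 128 youths (Data collection); difference 0.74, SD 1.48, ICC 0.05, 15–20 youths per service (Sample size and power calculation); fidelity scored 1 to 5, with 4 as sufficient (Model fidelity; Analyses, item 4).

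**Assumed, because the protocol gives no fidelity values.** The gap Δ between arm means and the within-arm SD s of the service scores.

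**1. The plan's own figure.** The protocol states no figure for the fidelity adjustment. Its sample size before clustering reproduces: n per group = 2 × (1.960 + 0.842)² × (1.48/0.74)² = 2 × 7.85 × 4 = 62.8, so 63. It is used below only to set the size of the effect.

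**2. Controls have no score.** In a complete-case fit all 128 control youths (of 251 at baseline; fewer of each at follow-up) are dropped. In the remaining rows the arm indicator is 1 throughout and equals the intercept column. The design (intercept, arm, fidelity) has rank 2 of 3, so the arm effect does not exist in that fit.

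**3. Controls have a score: precision.** With equal numbers of services per arm, r² between arm and fidelity is (Δ²/4)/((Δ²/4) + s²). The variance inflation is 1/(1 − r²) = 1 + Δ²/(4s²), and the standard error factor is its square root.

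| Δ | s | r² | Variance inflation | SE factor |
|---|---|---|---|---|
| 1 | 0.5 | 0.50 | 2.0 | 1.4 |
| 1 | 0.4 | 0.61 | 2.6 | 1.6 |
| 2 | 0.5 | 0.80 | 5.0 | 2.2 |
| 2 | 0.4 | 0.86 | 7.25 | 2.7 |
| 2.5 | 0.5 | 0.86 | 7.25 | 2.7 |
| 2.5 | 0.4 | 0.91 | 10.8 | 3.3 |

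**4. Controls have a score: what is estimated.** In a linear model, if a share π of the effect runs through fidelity, the adjusted arm coefficient targets (1 − π) × 0.74. That is 0.74 at π = 0, 0.37 at π = 0.5, and 0 at π = 1.

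**5. Simulation check.** Ten services of 18 youths, ICC 0.05, SD 1.48, true total effect 0.74, 4,000 repetitions, analysed at service level. The Houvast fidelity mean was 4 (SD 0.3–0.6). Controls were coded 0 or 1, or measured with mean 1.5–3 and SD 0.5. The arm-only standard error can be checked by hand: the variance of a service mean is 0.05 × 2.19 + 0.95 × 2.19/18 = 0.110 + 0.116 = 0.225, and √(2 × 0.225/5) = 0.30.

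| Truth and control value | Arm only: mean, SD, rejection | Arm + fidelity: median, SD, rejection |
|---|---|---|
| All through fidelity; coded 0 or 1 | 0.73–0.74, 0.30, 56–58% | 0.01–0.02, 1.4–3.6, 4–5% |
| All through fidelity; measured | 0.73–0.74, 0.31–0.38, 42–54% | about 0, 0.47–0.99, 5% |
| None through fidelity; coded 0 or 1 | 0.74, 0.29–0.31, 57–59% | 0.68–0.84, 1.4–3.6, 5–8% |
| None through fidelity; measured | 0.73–0.74, 0.30, 58–59% | 0.73–0.74, 0.48–0.96, 11–29% |

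The SD in the last column is half the distance between the 16th and 84th percentiles. The arm-only rejection rates reflect ten clustered services and serve here only as the comparator; the adequacy of the planned sample size is a separate matter.

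**The case against.** Several points on the other side have weight.

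- **Is fidelity scored only in Houvast services?** A reader might infer this as fact. The content of the audit and the Care as usual section point that way, and the Houvast section describes fidelity monitoring by internal coaches only in the intervention group. But no sentence excludes control services, and both the Model fidelity section and Analyses, item 4 speak of each service without restriction. It remains a strong inference.
- **Is the effect certainly not estimable?** That needs two things the protocol does not state: no value for controls, and a complete-case fit. Centring fidelity within the Houvast arm and setting controls to 0 would keep the arm effect estimable. No such coding is stated, though an analysis plan could contain one.
- **Is the arm effect always biased toward zero?** No. Where none of the effect runs through fidelity, the simulated estimates stay roughly centred on 0.74 and the harm is lost precision. If fidelity and outcome share service-level causes, the bias can go either way.
- **Would controls score near the bottom of the scale?** The documents do not support this. Indicators such as caseload ratio and community contact are generic, and usual-care services could score moderately. The 1-point gap in the table allows for that.
- **Is the adjusted model meant as secondary?** The covariate list is illustrative, item 2 has a second, exploratory purpose, and item 4's sentence is the only stated analysis of the association in research question 4. A secondary purpose is therefore plausible. But both sentences tie fidelity to the test of effectiveness, and nothing calls that model secondary or names an arm-only model as primary.

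These points limit how firmly the harm can be stated. None makes fidelity a valid confounder.

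**Conclusion.** The plan is wrong as written on this point: a service-level score that follows from allocation, and probably carries part of the effect, is adjusted for in the between-arm effectiveness model, with no stated value for controls.

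The consequence depends on facts the protocol does not give. With unscored controls and a complete-case fit there is no arm effect to estimate. With scored or coded controls, the arm effect is attenuated in proportion to the share that works through fidelity, down to about 0 if all of it does. If none does, power falls in the simulations from 57–59% to 5–29%. The standard error factors of 1.4 to 2.7 (3.3 at the widest gap and smallest SD tried) are illustrations under assumed gaps and SDs. That fidelity follows allocation does not depend on those values. Because the affected coefficient answers research question 1, this should be corrected before analysis.

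**What to change.** 1. In Analyses, item 2, remove model fidelity from the covariate list. Estimate effectiveness by allocated arm, adjusting for baseline covariates only.
2. In Analyses, item 4, reword the last sentence rather than delete it, so that research question 4 keeps an analysis: the association of fidelity with outcome is examined separately, as a secondary, exploratory analysis within the five Houvast services, for example by plotting service mean change against fidelity score.

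The cost is two sentences of wording and no new data. The drawback is that five service scores can describe the association only imprecisely. As a guide, a simple correlation of five points needs |r| above 0.88 for two-sided p < 0.05: t(0.975, 3 df) = 3.18, and 3.18/√(3.18² + 3) = 0.88. That limit comes from the number of Houvast services and is not created by the change.
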